### Blinding

Due to the particular nature of our study, only the outcome assessor is blinded. Participants are not blinded in the study.

### Inter-rater reliability

Reliability of the MFES [11], Short FES-I [13], PPA knee extension [34], TUG [44], 6MWT [45], SF-36v2 [46] and EQ-5D [47] have been established. However, we find no literature on the reliability of NCW test and decided to carry out a reliability assessment.

Test-retest reliability was then established between the outcome assessors, Intraclass Correlation Coefficient 0.972, from the analysis of 10 repeated timed walk of the NCW test.

### Statistical methods

Missing data will be analysed by intention-to-treat approach. Baseline measures for age, body mass index, MFES, TUG test, 6MWT, PPA knee extension strength, NCW test, SF-36v2 and EQ-5D will be analysed for normality. The primary outcome measure is the change in MFES score. Outcome measures will be quantitatively analysed with the mixed model for between group comparisons for statistically significant difference. Statistical significance is set at *p*(2-tailed) < 0.05. Clinical significance will also be analysed based on MCID or minimal detectable change for each of the outcome measures. The mean MCID will be obtained from participants who have a rating of 3 on the GROC scale.

### Health economic evaluation

The trend of rising healthcare cost is a concern to the population. Evaluation of the cost-effectiveness of the programme will determine the feasibility of implementing the programme as a fall prevention programme. The cost-effectiveness of the intervention programmes will be analysed at the end of one year follow-up. We will analyse the cost of programme, EQ-5D, fall history and incurred opportunity cost. The EQ-5D will provide the study with Quality-Adjusted Life Years. Fall history and accompanying opportunity cost will be obtained from telecommunication interview with the participant. Opportunity cost of a fall is equivalent to the total cost of treatment and management for the fall. The limit for overall cost per fall prevented is set at S$20,000 to evaluate the programme cost effectiveness.

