## Methods

### Design

This is a parallel prospective single-blind randomised active-control trial. The ratio of subjects in each group is 1:1; refer to Figure 1 for the flow of participants in our study (week 0 to week 13). Each participant who completes the week 13 follow-up will be given a pedometer to track daily physical activity from week 13 to 24 and a final assessment is conducted on week 24. During the first 13 weeks, participants report weekly on incidence of falls to the interventionist. From week 14 to 52, participants record incidence of fall on a falls history sheet kept at home and to report the falls to the Principal Investigator or the outcome assessor immediately. The outcome assessor will contact the participants monthly from week 14 to 52 to update on any fall incidence.

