### Outcomes

The outcome measures are assessed one week before the first intervention session (week 0), one week after the last intervention session (week 13) and a final reassessment on week 24 by an independent blinded outcome assessor (Table 2). The primary outcome of this study is an improvement in fall efficacy with the Modified Falls Efficacy Scale (MFES). New recent falls after the initiation of intervention will investigate the success of the programme in falls prevention. This is carried out by self report of falls by the participants via telecommunication and on a falls recording sheet. The secondary outcomes of this study are improvement in knee extensor strength, endurance, agility, functional status and quality of life. The global rating of change (GROC) scale is used to assess the participant's perceived change from baseline on each follow-up [32,33].

**Table 2 T2:** Data collection time-points

Data	Baseline	Week 13	Week 24	Week 52
Demographics	**X**			
Fall history	**X**	**X**	**X**	**X**
Fall risk (PPA)	**X**	**X**		
Frailty (SPPB)	**X**	**X**		
Fall efficacy (MFES, Short FES-I)	**X**	**X**	**X**	
Strength (knee extension)	**X**	**X**	**X**	
Endurance (6MWT)	**X**	**X**	**X**	
Agility (TUG)	**X**	**X**	**X**	
Dynamic balance (NCW)	**X**	**X**		
Gait speed (4 m walk)	**X**	**X**	**X**	
Quality of life (SF-36v2*, EQ-5D)	**X**	**X**	**X**	
Participant's perceived change (GROC)		**X**	**X**	
Home exercises (Exercise diary)		**X**		
Physical activity (Pedometer)			**X**	

*Week 24 SF-36v2 components assessed are physical function and bodily pain

Fear of fall (self efficacy): MFES is a validated 14-item questionnaire of fall efficacy of the older person in various ADLs and community activities [11]. It is administered by an interviewer approach in our study to prevent misinterpretation by the participant and to maintain consistent and accurate responses from the participant. The Short Fall Efficacy Scale -- International questionnaire takes a shorter time to administer with 7-item on indoor and outdoor activities [13]. The questionnaires have no risk of recall bias as they require the participants to rate their perceived confidence based on the day of assessment.

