### Follow-ups

On the 13^th ^week, each participant undergoes an outcome assessment. After the assessment, the participant will be issued a pedometer (HJ-109 Omron Healthcare, Japan) for daily quantifying of physical activity via number of steps taken for the day [43]. Participants in both groups will continue with the home exercises after the last supervised exercise session. The pedometer is used to gauge and encourage physical activity of the participants. A follow-up monitoring of change on the 24^th ^week will assess changes in self efficacy, impairments, functional changes and quality of life. Monthly from week 14 to 52, the participants will be contacted for any events of fall. The pedometer reading will be correlated with the change in outcome measures from week 13 to 24.

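### The one-year cost-effectiveness analysis takes its QALYs from EQ-5D, but EQ-5D is last measured at week 24, which leaves 28 of 52 weeks without utility data

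*Protocol article*

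**What the plan says.** On timing, the Health economic evaluation section states: "The cost-effectiveness of the intervention programmes will be analysed at the end of one year follow-up". It lists EQ-5D among the inputs and adds: "The EQ-5D will provide the study with Quality-Adjusted Life Years". No other source of utilities is named.

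On data collection, the Table 2 row that begins "Quality of life (SF-36v2*, EQ-5D" is marked at baseline, week 13 and week 24 and is blank at week 52. The only row marked at week 52 is fall history. The text agrees with the table: the Design section says "a final assessment is conducted on week 24", and the Outcomes section refers to "a final reassessment on week 24 by an independent blinded outcome assessor".

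After week 24 the planned contacts concern falls. The Follow-ups section says "Monthly from week 14 to 52, the participants will be contacted for any events of fall", and the economic section says "Fall history and accompanying opportunity cost will be obtained from telecommunication interview with the participant". Neither mentions EQ-5D.

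The one economic threshold given is for falls: "The limit for overall cost per fall prevented is set at S$20,000 to evaluate the programme cost effectiveness". There is no threshold for cost per QALY.

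**The concern.** A QALY total is the area under a utility curve over a stated period. If that period is the year for which the analysis is announced, the curve has no measured point in its last 28 weeks, and the between-group difference there depends on what the analyst assumes.

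If the QALY is cut off at week 24 instead, a cost-per-QALY ratio would combine one year of costs with less than half a year of health effect. A fall between weeks 24 and 52 would enter the fall count and the costs, but its effect on quality of life would not be measured. For a falls programme, that is one of the main ways in which later QALYs could differ between the arms.

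Utilities that were not collected cannot be recovered later, and an analysis plan cannot supply them. SF-36v2 does not fill the gap: it too has no week 52 assessment, and a footnote to Table 2 reduces it to two components at week 24.

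**Working it through.** The document gives no figure for QALY coverage, so there is none to reproduce.

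**Inputs from the document**
- EQ-5D at weeks 0, 13 and 24 (Table 2).
- Analysis at the end of one-year follow-up, taken as 52 weeks (Health economic evaluation; last column of Table 2).

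**Share of the year without utility data**
- (52 − 24)/52 = 28/52 = 53.8%.
- If baseline lies one week before week 0: 28/53 = 52.8%.
- If the year is counted from week 1: 28/51 = 54.9%.

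The share is above one half on each reading.

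**Sensitivity of a one-year QALY difference**

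Assumption, not from the document: the between-group utility difference is 0 at baseline, rises linearly to *d* at week 13 and is still *d* at week 24. By the trapezoidal rule, in QALYs:
- Observed part, weeks 0 to 24: *d* × (13/2 + 11)/52 = 17.5*d*/52.
- Full persistence to week 52 adds 28*d*/52, total 45.5*d*/52.
- Linear fade to zero at week 52 adds 14*d*/52, total 31.5*d*/52.
- Immediate loss after week 24 adds nothing, total 17.5*d*/52.

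With *d* = 0.05, chosen only for illustration:

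| Assumption for weeks 24–52 | One-year QALY difference | Relative to immediate loss |
|---|---|---|
| Full persistence | 0.044 | 45.5/17.5 = 2.6 |
| Linear fade to zero | 0.030 | 31.5/17.5 = 1.8 |
| Immediate loss | 0.017 | 1.0 |

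*d* cancels from the ratios, so they do not depend on the size of the effect. They do depend on the assumed shape of the curve up to week 24.

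**What depends on the missing data**

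| Result | Data needed | Collected to week 52? |
|---|---|---|
| Cost per fall prevented | Programme cost, falls, fall costs | Yes: falls to week 52, fall costs by interview |
| One-year QALYs, cost per QALY | EQ-5D over the year | No: stops at week 24 |

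**The case against.** The strongest objection is that the article does not say in so many words that QALYs run over 52 weeks. Analysing at the end of one year can describe when the analysis is run, and a 24-week QALY is not excluded. This stands as a limit on certainty. It does not remove the problem, because a 24-week QALY beside one-year costs and falls is itself a mismatch unless the costs are cut to the same period.

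A second objection is that a journal article may leave the QALY horizon, the area-under-the-curve method and any extrapolation rule to the full protocol or an analysis plan. That is right, and their absence is not criticised here. The point is the conflict between the announced timing of the analysis and an explicit schedule that has a week 52 column and leaves EQ-5D blank in it.

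A third objection is that the 2.6-fold range compares two extremes of an assumed trajectory. That also stands. A reader might infer that the trial's QALY result would be wrong by such a factor, but the documents give no utility data from which an error could be estimated.

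Finally, a reader might infer that the whole economic evaluation fails at one year. The documents do not support that: the only stated criterion is cost per fall prevented, and it needs no utilities.

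**Conclusion.** The inconsistency is real and narrow. On the natural reading, a one-year QALY is announced while 28 of 52 weeks (54%) have no utility measurement, so the result would rest on an extrapolation assumption. On the other reading, 24-week QALYs would stand against 52-week costs and falls. The range of up to 2.6-fold holds for a utility difference that is zero at baseline and constant from week 13, and it indicates sensitivity only.

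The issue is moderate. It is confined to the QALY part of a secondary analysis. The MFES primary outcome, the sample size built on it, the falls follow-up and the S$20,000 per fall prevented criterion are untouched.

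**What to change.** **Preferred.** Mark EQ-5D at week 52 in Table 2 and have the blinded outcome assessor administer it in the final monthly contact, which is already planned. Compute QALYs by area under the curve over weeks 0, 13, 24 and 52. The utility between weeks 24 and 52 would still be interpolated, but between two measured points.

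The cost is an amendment and a few extra minutes per call. If the contact is by telephone, the mode of administration at week 52 differs from the clinic assessments, though equally in both arms. Participants may speak English, Mandarin or local dialects, so suitable language versions and interviewers are needed.

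**If that is not possible.** State that QALYs and their matching costs are limited to 24 weeks, and report only cost per fall prevented at one year. This needs no new data, but it gives up a one-year QALY result.

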### Time-line

The study time-line is monitored by the study principal investigator. Table 3 reflects the milestones of the study.

**Table 3 T3:** EFFECT milestones

Time-line	Events
Jan 2009	Gym-based group exercises for the older population developed
Jul 2009	Randomised controlled trial planned
Aug 2009	SHF Research grant submitted
Feb 2010	Research grant awarded
Jun 2010	Study commenced
Jul 2010	Recruitment commenced
Mar 2011	Recruitment completed
Jun 2011	Last 12-week follow-up
Sep 2011	Last 24-week follow-up
Oct 2011	Data analysis completed
Nov 2011	Publication submitted

SHF: SingHealth Foundation

## Discussion

The EFFECT study is the first randomised active-control trial evaluating the reduction of fear of falling and self-reported falls between the Nintendo Wii and the standard intervention. The intervention in this study undertakes a multimodal approach in rehabilitation that is in accordance with evidence-based practice [16,18-20,22,24,48].

The WiiActive game is beneficial for the older person with strength, cardiovascular, balance and coordination exercises [17]. The band exercises may be more readily accepted as compared to stack weights and free weights. Majority of the older people are frail and cannot jog in the WiiActive game. Modified instructions to march on the spot will allow them to complete difficult exercises and improve confidence. Balance training with the WiiFit board is achieved through activities that require the participant to avoid obstacles in activities such as roller-skating. Progression to a combination of balance and coordination training that involves upper limb and lower limb movements is practised with virtual tennis simulation.

In the clinical setting, the potential use of gaming with visual feedback can facilitate the reduction of physical time that the therapist has to spend with the patient. Short-term visual feedback rehabilitation has also been found effective in improving functional status [27]. Furthermore, the exercises when done in a group can enhance compliance and improve motivation [49].

The minor disadvantage of the WiiActive game is the requirement the controller be held by the participant for the system to register movement patterns. This can be overcome if game developers utilise the WiiMotion-Cam technology that allows a controller-free interface.

The unique feature of the group exercise programme is the component of specific modalities for participant based on the initial assessment. This is to ensure that the major issues and goals raised by the subjects are treated and achieved within the 12 weeks of intervention.

Our study aims to achieve fall prevention and improving confidence of older adults in performing ADLs. The study investigates if the use of virtual feedback gaming will achieve these outcomes superior to a standard rehabilitation model.

## Abbreviations

ADLs: Activities of daily living; TUG: Timed up and go; 6MWT: 6-minute walk test; NCW: Narrow corridor walk; SF-36v2: Short Form -- 36 version 2; EQ-5D: European Quality of Life -- 5 dimensions; SGH: Singapore General Hospital; SPPB: Short Physical Performance Battery; ICH: International Conference on Harmonisation; GCP: Singapore Guidelines for Good Clinical Practices; PPA: Physiological Profile Assessment; MFES: Modified Falls Efficacy Scale; GROC: Global rating of change; MCID: Minimum clinically important difference;
